## Abstract

**Background:**

Clinicians often apply heating or cooling stimulation for treatment of musculoskeletal pain. However, scalding, frostbite and skin ulcers may occur from the excessive use of either therapy alone. Heating and cooling combination therapy may be a suitable alternative for treatment of musculoskeletal diseases, although insufficient research has documented the safety and efficacy of such therapy. The purpose of this clinical trial is to determine the efficacy and safety of heating and cooling combination therapy for treatment of chronic low back pain.

**Methods/Design:**

This is a multicenter, parallel-group, double-blinded, randomized controlled trial to evaluate the efficacy and safety of a heating and cooling combination therapeutic device (OCH-S100) in patients with chronic low back pain. Eighty participants with chronic low back pain will be recruited from two hospitals in South Korea (Dongguk University Ilsan Oriental Hospital and Dongguk University Bundang Oriental Hospital). Enrolled patients will be randomly divided into a treatment group and a sham group. Patients in both groups will be given 10 treatments (15 min per treatment) over 4 weeks. The protocol will consist of five cycles of heating/cooling therapy (maximum: 45 °C, minimum: 15 °C) in the treatment group, and five cycles of sham therapy (maximum: 1 °C above skin temperature, minimum: 1 °C below skin temperature) in the sham group. The primary outcome measure is change from baseline in the 100 mm Visual Analogue Scale (VAS) for pain after 4 weeks. There are six secondary outcome measures that consider disability or range of motion (ROM).

**Discussion:**

This research will determine the efficacy and safety of heating and cooling combination therapy on chronic low back pain. The results of this trial may have important implications for the more widespread use of heating and cooling combination therapy for treatment of musculoskeletal pain.

**Trial Registration:**

NCT02289170 (14 October 2014)

## Background

Heating and cooling therapies are widely used to treat musculoskeletal pain [1]. For example, in the United States, 75 % of patients with low back pain are treated with heating therapy and 7 % with cooling therapy [2].

Heating therapy increases tissue temperature, blood flow, metabolism and connective tissue extensibility [1]. There are also reports that heating therapy increases the activity in all of the Ia and many of the Ib afferents, decreases the activity of most group II spindle afferents, decreases muscle spasms, and increases the speed of nerve conduction [3]. Other studies indicated that heating therapy is more effective than placebo in relieving pain, decreasing disability, decreasing muscle tension, and improving range of motion [4, 5].

There is evidence that cooling therapy decreases tissue blood flow due to vasoconstriction, and that it also reduces tissue metabolism, oxygen utilization, and inflammation [1, 6]. Cooling therapy decreases the velocity of nerve conduction in superficial tissues by slowing the firing of muscle spindle afferents and reflex responses, thus decreasing muscle spasms and pain [7]. Use of cooling therapy for musculoskeletal problems can also reduce intake of painkillers because it reduces pain and body fluid penetration [8].

However, the overuse of cooling therapy or heating therapy due to physiological adaptation can lead to skin damage such as scalding, frostbite, and ulcers [1, 6]. We developed a heating and cooling combination therapy device (OCH-S00) that reduces the probability of skin damage. This device maximizes the stimulation and reduces the potential harm from heating and cooling by use of a probe to reduce sensory adaptation.

Thermo-receptors are sensitive to different temperatures. Thus, TRPA1 is mainly responsible for painful cold sensation below 18 °C, TRPM8 for cool sensation at 23 to 28 °C, TRPV2 for warm sensation at 30 to 39 °C, and TRPV1 for painful hot sensation above 43 °C [9]. The heating and cooling device described here stimulates the cold, cool, warm and hot receptors by applying temperatures in the range of 15 to 45 °C, well below the burn point. Thus, this device is expected to have anti-inflammatory effects, increase muscle relaxation, decrease edema and provide pain relief, without damaging the skin.

The purpose of this research is to evaluate the safety and efficacy of the OCH-S100 heating and cooling combination therapy device on patients with chronic low back pain.

## Methods/Design

### Study design

This research of the clinical efficacy and safety of heating and cooling combination therapy is a multicenter, randomized, double-blinded, parallel-group study. All enrolled subjects are patients with chronic low back pain. This research protocol was externally peer reviewed by Korean Ministry of Food and Drug Safety (KMFDS) and Korean Health Industry Development Institute (KHIDI). Two clinical research centers in Korea will participate in this trial: Dongguk University Ilsan Oriental Hospital and Dongguk University Bundang Oriental Hospital. This research protocol was approved by Dongguk University Ilsan Oriental Hospital’s Institutional Review board (IRB) and Dongguk University Bundang Oriental Hospital’s IRB. Each subject will provide informed consent before enrollment.

### Recruitment

Participants will be recruited through advertisements in local newspapers and on bulletin boards at each trial center. The target sample size is 80 subjects. Telephone screening will be performed before the trial to determine if subjects fulfill the selection criteria. Final enrollment will be determined by an orthopedist and a radiologist through physical exams, radiological tests, blood and urine tests, and relevant questionnaires.

### Participants

All outpatients who are 20 to 75 years of age and have suffered from low back pain in the previous 3 months or more and had ratings over 40 mm on a 100 mm Visual Analog Scale (VAS) for pain will be screened. Subjects will be excluded if any of the following are present: (i) trauma or surgery in the lumbar region in the 6 months prior to enrollment; (ii) low back pain accompanied by sciatica; (iii) systemic disease or severe dysfunction due to another medical problem (cancer, infection, *etcetera*); (iv) history of using medication(s), traditional oriental medical care, or physiotherapy for treatment of low back pain in the 4 weeks prior to enrollment; (v) neurological disease, such as topical or whole body hypoesthesia, that may affect temperature sensation (stroke, peripheral neuropathy, *etcetera*); (vi) hypersensitivity to heating and cooling stimulation; (vii) pregnancy or lactating; or (viii) participation in other clinical trials in the 3 months prior to or after enrolling in this trial.

### Randomization and blinding

Randomization will be performed by an independent statistician using a computerized random-number generator through the block-randomization method of SAS version 9.1 (SAS Institute Inc. Cary, NC, USA). Separate randomization files will be created for each study site. Allocation concealment will be maintained by use of opaque sealed envelopes. After the researcher screens a patient for inclusion and receives signed informed consent, the next envelope in the sequence will be accessed and opened by the certified Korean Medicine Doctor who supervises the medical device, immediately prior to treatment. A total of 80 participants will be randomly and blindly assigned to a treatment group or a sham group. All subjects, practitioners, and the outcome assessor will be blinded to group assignment. Blinding of the certified Korean Medicine Doctor who supervises the medical device and sets up the treatment (medical equipment manager) is not possible. The patients will be told: “You will be treated with one of two heating and cooling combination treatments. One has a large range of temperature change and the other has a small range of temperature change.”

### Treatment and assessment

Subjects in both groups will be treated 10 times over 4 weeks. The treatment term of 4 weeks was based on previous studies of the treatment of general chronic low back pain [10]. Each treatment will be 15 min and there will be two to three treatments per week, based on the protocol of previous research on heating and cooling combination treatment [11]. The outcome assessor (who does not participate in the treatment) will measure the degree of pain sensitivity by pressing eight acupoints (four on each side of the waist; BL23, BL24, BL25, and BL26) that are frequently used to assess low back pain [12–16]. This assessment will employ a pressure algometer, with a circular and flat probe of 1 cm diameter (Commander Algometer, JTECH Medical, Midvale, Utah, USA), to identify the two most painful acupoints. Before treatment, the medical equipment manager will measure the skin temperature of each patient in the treatment and sham groups using thermometer (Superfast Thermapen Pro-surface, ETI, England) (Table 1).

**Table 1 Tab1:** Content of outcome measurement

	Treatment Number											
Outcome measure	B	1	2	3	4	5	6	7	8	9	10	F
Primary outcome												
VAS	X	X	X	X	X	X	X	X	X	X	X	X
Secondary outcomes												
KODI		X					X				X	X
KRMDQ		X					X				X	X
TMBQ		X					X				X	X
Modified Schöber test		X					X				X	X
Finger-to-floor distance		X					X				X	X
Finger-to thigh distance		X					X				X	X

*B* baseline, *F* follow-up, *VAS* Visual Analog Scale, *KODI* Korean Oswestry disability index, *KRMDQ* Korean Roland Morris Disability Questionnaire, *TMBQ* Traditional Medicine Back pain Questionnaire

#### Heating and cooling combination therapy

The patients in this group will receive heating and cooling combination therapy. The probe is attached to the acupuncture points for 15 min, and its temperature will be cycled five times, from the maximum of 45 °C to the minimum of 15 °C. This temperature range was chosen to provide stimulation of cold, cool, warm and hot receptors.

#### Sham therapy

The patients in this group will receive sham heating and cooling combination therapy under identical conditions, except for probe temperature. The probe’s temperature will be cycled five times, from 1 °C above skin temperature to 1 °C below skin temperature.

During the 4-week study, patients will be prohibited from using any treatment that could influence the results, such as analgesics, nonsteroidal anti-inflammatory drugs, muscle relaxants, oral corticosteroids, antidepressants, steroid injections, high frequency heat coagulation, physiotherapy, acupuncture, moxibustion and surgery. Patients who use any of these treatments will be excluded. All patients will be questioned about medication usage during each treatment session.

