### Analysis of data

A VAS will be used to assess the effect of treatment. The primary endpoint is the change in the 100 mm Pain VAS from baseline (before treatment) to 4 weeks [10, 12, 17]. The 100 mm VAS is widely used because it provides reliable and valid measurements of pain intensity [18]. Each patient will be asked to check their pain intensity along an ungraded 100 mm horizontal line, where ‘0’ represents ‘no pain’ and ‘100’ represents ‘unbearable pain’.

The secondary endpoints are change from baseline in three evaluations of functional disability (Korean Oswestry disability index [KODI], Korean Roland Morris Disability Questionnaire [KRMDQ], and Traditional Medicine Back pain Questionnaire [TMBQ]) and three evaluations of range of motion (ROM) (modified Schöber test, finger-to-floor distance, and finger-to-thigh distance). These parameters will be measured at baseline, 2 weeks, 4 weeks, and at 4 weeks after the last treatment.

The KODI has 10 criteria related to daily living activities and each item has six possible responses, ranging from ‘no problem’ to ‘not possible’. The KODI focuses on a limitation in the range of physical functions, including standing, walking, lifting, sitting, lying down, dressing, and personal care [18]. We excluded questions about sexual activities because many subjects do not provide honest answers about their sex lives, and it is hard to account for subjects who are single. The KRMDQ contains 24 yes/no queries and also focuses on limitations in physical functions, including walking, bending over, sitting, lying down, dressing, sleeping, self-care, and daily activities. The KRMDQ is easy to understand, interpret and score. Higher scores in the KRMDQ and KODI indicate greater disability [18]. We will use Korean versions of these surveys, which have documented reliability and validity [19, 20]. The TMBQ evaluates low back pain and is based on traditional Korean medicine [21].

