### Sample size

The primary endpoint will be change in 100 mm VAS score after 4 weeks of treatment. Liu *et al*. [25] previously showed that the 4-week change was 7.6 for the test device and 3.9 for the control device. Patients will be randomized to the test and sham groups in a 1:1 ratio. Assuming a reference standard deviation (SD) of 5.37, power analysis indicates that a sample size of 34 has an 80 % probability of yielding a significant difference at the level of 0.05. In order to achieve stronger results, a one-sided 97.5 % lower confidence limit for the treatment difference (VAS on test device - VAS on sham device) will be greater than 0. We will allow for a 15 % dropout rate by randomization of 40 subjects to each group.

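### Excluding randomised patients who use a prohibited treatment selects on an event related to pain and leaves the primary comparison liable to bias

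*Protocol article*

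**What the plan says.** Under Sham therapy, in a paragraph that covers both arms, the protocol article sets a ban and a consequence. The ban: "During the 4-week study, patients will be prohibited from using any treatment that could influence the results", followed by a list running from analgesics and NSAIDs to acupuncture and surgery. The consequence: "Patients who use any of these treatments will be excluded". Use is checked throughout: "All patients will be questioned about medication usage during each treatment session".

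Three other places fix when the rule acts.

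- Randomization and blinding: the allocation envelope is "opened by the certified Korean Medicine Doctor who supervises the medical device, immediately prior to treatment". Anyone questioned at a treatment session is therefore already randomised.
- Participants, criterion (iv): use before the trial has its own baseline exclusion, which ends with "physiotherapy for treatment of low back pain in the 4 weeks prior to enrollment". The Sham therapy sentence does not restate it.
- Analysis of data: "The primary endpoint is the change in the 100 mm Pain VAS from baseline (before treatment) to 4 weeks". The ban covers the period up to the primary time point.

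Sample size adds a general allowance: "We will allow for a 15 % dropout rate by randomization of 40 subjects to each group". Statistical analysis names ANCOVA with a site effect and Student's t-test. It does not mention patients excluded under the Sham therapy rule.

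**The concern.** Randomisation makes the two groups comparable only as long as the groups analysed are the groups randomised. Here a patient can leave the comparison because of something that happens after allocation. That event is plausibly linked to the outcome: patients enter with VAS above 40 mm and no back-pain treatment in the previous 4 weeks, and someone who then takes an analgesic is likely to be someone whose pain has not eased. The frequency may also differ by arm, since one arm receives 15–45 °C cycling and the other 1 °C either side of skin temperature.

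Two opposite distortions are possible. If the device works and sham patients turn to other treatment more often, the poorest sham results disappear and the effect is diluted. If users are more common in the active arm, its poorest results disappear and the device looks better than it is. The 15 % dropout allowance protects the number of patients, not the comparability of those who remain.

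**Working it through.** **Inputs from Sample size and Statistical analysis.** Mean change 7.6 (test) and 3.9 (sham), difference 7.6 − 3.9 = 3.7; SD 5.37; two-sided 0.05; 80 % power; 34 per arm, 40 after 15 % dropout.

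**1. The plan's own figure.** n per arm = 2(1.96 + 0.8416)² × 5.37² / 3.7² = 33.07, rounded up to 34; 34 / 0.85 = 40. Both stated figures reproduce. Power from the t distribution is 79.9 % at 34 per arm and 86 % at 40. The sample size calculation is not at fault.

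**2. A true effect, with exclusion below one cut-off common to both arms.** The document gives no exclusion rates, so these are assumed. Let p be the share of sham patients excluded.

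- Cut-off: c = 3.9 + 5.37 × z(p).
- Share of test patients excluded: Φ((c − 7.6)/5.37).
- Mean of those who remain in an arm: mean + SD × φ(a)/(1 − Φ(a)), where a is the standardised cut-off in that arm.

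Worked for p = 20 %: z = −0.842, so c = −0.62. In the test arm a = (−0.62 − 7.6)/5.37 = −1.531, which excludes 6.3 %. The multipliers are 0.350 (sham) and 0.132 (test). The remaining means are 3.9 + 5.37 × 0.350 = 5.78 and 7.6 + 5.37 × 0.132 = 8.31, a difference of 2.53.

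| Sham excluded | Test excluded | Expected difference | Power |
|---|---|---|---|
| none | none | 3.70 | 86 % |
| 10 % | 2.4 % | 2.97 | 75 % |
| 15 % | 4.2 % | 2.73 | 70 % |
| 20 % | 6.3 % | 2.53 | 64 % |

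Power in the three exclusion rows is from 20,000 simulated trials each, t-test, 40 randomised per arm.

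**3. A softer link.** A hard cut-off on the final change is the extreme case. With overall exclusion (both arms together) of 5, 10 and 15 %, the hard cut-off leaves differences of 3.07, 2.71 and 2.44. A logistic link between poor response and use leaves 3.35, 3.14 and 2.97. The dilution is smaller but does not vanish.

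**4. No true effect.** The mean of those who remain after the worst p are removed rises by φ(z)/(1 − p) SD: 0.2332/0.85 = 0.274 for p = 15 % and 0.1031/0.95 = 0.109 for p = 5 %. Removing 15 % from one arm and 5 % from the other shifts the difference by about 0.166 SD, or 0.166 × 5.37 ≈ 0.89 on the VAS. Two-sided type I error is about 12 % with population cut-offs and about 15 % if exactly 6 and 2 of 40 are removed. The fixed-count version also understates the standard error, so 12 % is the better guide. With 15 % removed below the same cut-off in both arms, the shift is zero and type I error stays at about 5 %.

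**The case against.** **The key word is ambiguous.** The sentence does not say what patients are excluded from (treatment, trial or analysis), and Statistical analysis drops nobody. That stands as a limit on the wording. It does not remove the point: after withdrawal the week-4 VAS is not collected, and after removal from the analysis it is not used. Only a reading confined to study treatment, with assessment continuing, would be harmless, and the text does not state it.

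**Analysis sets may be defined elsewhere.** True, and the article's silence on an intention-to-treat set is no finding. The point rests on a stated rule. An analysis plan can define a set of all randomised patients, but it cannot supply measurements that the rule prevented.

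**Stronger readings that the document does not support.**

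- A reader might infer that the rule does bias the result, or that it flatters the device. Neither can be derived: the direction depends on which arm uses more.
- A reader might infer that the confidence interval and p-value always lose their stated error rates. With no true effect and equal exclusion they do not.
- A reader might take 34 of 40 as evidence that users are to be dropped. Sample size calls it dropout and does not link it to prohibited treatment.
- A reader might count criterion (viii), on other trials, as a second case. It stands in the eligibility list, and nothing links it to pain, to arm or to removal from the analysis.

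**Keeping users has its own cost.** This is the strongest objection. The 86 % benchmark assumes that the banned treatments do not affect VAS, yet they are banned because they might. In the 20 % sham scenario, if users improve by an assumed 10 mm, keeping everyone gives 3.7 − 10 × (0.200 − 0.063) = 2.3 and power of 68 %, against 2.5 and 64 % with exclusion. At 5 mm it gives 3.0 and 83 %; at 15 mm, 1.6 and 35 %. So the fix does not reliably restore 3.7 or 86 %. What it does is keep the randomised comparison intact and make its meaning clear.

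**Conclusion.** The point holds as a liability to bias. The document states a post-randomisation exclusion triggered by an event plausibly driven by the primary outcome, and nothing in Analysis of data, Sample size or Statistical analysis offsets it.

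The sizes are illustrations. They use the plan's means and SD, normally distributed changes and assumed exclusion rates. On that footing, expected dilution is from 3.7 to about 3.0–2.5, with power of about 75–64 % against about 86 % if all 40 per arm are analysed and co-treatment has no effect on VAS. Less strict links between pain and use give less dilution. A type I error of about 12–15 % needs unequal exclusion (15 % against 5 %) with no true effect.

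**What to change.** State that use of a prohibited treatment is recorded as a protocol deviation and does not remove a randomised patient from outcome assessment or from the primary analysis. Collect the week-4 VAS on every randomised patient regardless of use, and analyse each in the randomised arm with the ANCOVA already planned. Keep the set without prohibited treatment as a per-protocol sensitivity analysis, and report the number of users by arm.

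The ban itself is not at issue, nor is whether study treatment continues after such use; the sponsor should only make clear which of these the word in the Sham therapy section refers to.

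The cost is a wording amendment and one assessment that is already scheduled. The real downside is that the estimate will include any effect of co-treatment, which may itself dilute the difference. The result should therefore be described as the effect regardless of prohibited-treatment use. Recruitment was under way when the article was written, and week-4 values not collected cannot be recovered, so the change should come early.

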### Safety assessments

Any physical or clinical changes will be reported by the assessor, practitioner, and patient at each visit. All symptoms, date of onset, and duration will be recorded.

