### Statistical analysis

All data will be analyzed using SAS version 9.1 (SAS institute Inc. Cary, NC, USA). All statistical tests will be two-sided, and the level of significance will be set at 0.05. Continuous variables will be expressed as means ± SDs and categorical variables as numbers and percentages. For analysis of the primary endpoint, the two-sided 95 % confidence interval will calculated by analysis of covariance (ANCOVA) and the model will include fixed-effect for study site. Student’s *t*-test will be used for evaluation of primary and secondary end-points. Categorical data will be analyzed using Pearson’s chi-square test or Fisher’s exact test, as appropriate.

For safety analysis, the numbers and percentages of patients will be presented in a frequency table. Patients with adverse events will be listed along with their medical histories and concomitant medications, with start and stop dates. Categorical variables will be summarized by frequency tables, and continuous laboratory variables, and changes from baseline will be expressed by summary statistics. In addition, the number and percentage of patients with each value below, within and above the normal range will be tabulated, and “shift tables” (summaries of individual changes in laboratory parameters) will be generated.

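### The co-treatment ban covers drug and non-drug care and excludes users, but the check stated at each session asks only about medication

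*Protocol article*

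**What the plan says.** The co-treatment rule stands in the second paragraph of the protocol article's Sham therapy section and applies to both arms. It has three parts.

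- **The ban.** During the 4-week study, "patients will be prohibited from using any treatment that could influence the results". The list of examples mixes drugs with other care and ends with "steroid injections, high frequency heat coagulation, physiotherapy, acupuncture, moxibustion and surgery".
- **The consequence.** "Patients who use any of these treatments will be excluded".
- **The check.** "All patients will be questioned about medication usage during each treatment session".

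Two other places touch on what is recorded during the trial. Under Safety assessments, "Any physical or clinical changes will be reported by the assessor, practitioner, and patient at each visit". Under Statistical analysis, patients with adverse events are "listed along with their medical histories and concomitant medications, with start and stop dates".

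**The concern.** A rule that removes patients for using a treatment needs a way to find that use. Here the rule reaches drug and non-drug care, but the question said to be put to patients reaches drugs only. A patient who takes an analgesic would be asked about it and excluded. A patient who has acupuncture, or who uses a heat pack at home, would not be asked.

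The primary endpoint is change in pain VAS from baseline to 4 weeks, and the intervention is itself thermal. The sham stays within 1 °C of skin temperature. The Background cites studies in which "heating therapy is more effective than placebo in relieving pain", so home heat is close in kind to the treatment under test. If non-drug co-treatment began after baseline and went unrecorded, exclusions would fall mainly on drug users, and the report could not say whether other co-treatment was balanced between arms.

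**Working it through.** The plan gives no figure on this point, so the check is a comparison of texts.

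**Step 1: sort the named examples.**

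| Type | Items | Count |
|---|---|---|
| Drug | analgesics, NSAIDs, antidepressants, muscle relaxants, corticosteroids by mouth, steroid injections | 6 |
| Non-drug | acupuncture, moxibustion, physiotherapy, surgery, high-frequency heat coagulation | 5 |

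6 + 5 = 11 named examples. The medication question can reach the first 6. It does not, as worded, reach the other 5. This counts list items and does not measure risk. Self-applied heat or cold is on neither row; it is banned only through the open wording before the list.

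**Step 2: look for another in-trial check on non-drug care.**

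| Place in the protocol article | What it covers | Non-drug co-treatment during the trial? |
|---|---|---|
| Participants, exclusion (iv) | drugs, traditional care and physiotherapy for the back in the 4 weeks before enrolment | No; entry only |
| Sham therapy | question on medication at each session | No |
| Safety assessments | physical or clinical changes at each visit | No; symptoms, not treatments |
| Statistical analysis | concomitant medications, for patients with adverse events | No |
| Quality assurance | standardized recording forms, content not given | Not known |

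**Step 3: ask what would come to light anyway.** With two to three visits a week, surgery or heat coagulation would probably be noticed. That leaves physiotherapy, acupuncture, moxibustion and home heat or cold. Volunteered disclosure is less dependable here, because Quality assurance limits talk between practitioner and patient to the reporting of side effects. The wording of the set question therefore matters more.

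**Step 4: ask what better detection would do under the existing rule.** If the question were widened and nothing else changed, more patients would be excluded after randomization. Those exclusions depend on behaviour during treatment and could differ between arms, which can bias the comparison. The exclusion sentence therefore has to change with the question. The article does not say whether exclusion means withdrawal from follow-up or removal from the analysis. If it means withdrawal, such patients may have no 4-week VAS to analyse.

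**The case against.** The strongest objection is that this is a journal article, which condenses a fuller protocol. It does not say that the medication question is the only check, and asking about medication does not contradict a wider ban. The exact wording of a session question belongs on a case report form, and Quality assurance promises recording forms that are not shown. This stands as a limit on the finding: a reader might infer that the trial has no check on non-drug treatment, and the documents do not support that. They show only that the check the article states is narrower than the rule beside it. The article did choose to give the content and frequency of the check, so the mismatch is a fair point of wording.

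A second objection also has force. Exclusion (iv) removes anyone who used traditional Korean care or physiotherapy for the back in the 4 weeks before enrolment. Those enrolled are thus recent non-users, and starting such care within 4 weeks is less likely than in unselected patients. It remains possible, and the criterion does not name home heat or cold.

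A reader might also infer a biased result, for instance because sham patients who feel little temperature change seek heat elsewhere. Patients are told that one treatment has a large temperature range and the other a small one, so the idea is plausible. But the documents give no rate of use, no effect of such use and no split by arm. The Background's figure on heat therapy in the United States describes treatment there in general and is not a rate of home use in this trial.

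**Conclusion.** The point holds as a mismatch within one paragraph: a ban and exclusion rule that cover drug and non-drug care, served by a stated question on medication alone. As worded, non-drug co-treatment may go unrecorded while drug users are excluded. It is a minor point, worth acting on because the remedy is cheap.

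No figure in the plan is wrong, and neither the size nor the direction of any effect on the VAS comparison can be derived from the documents. The conclusion assumes that the question is put to patients as the article words it. If the forms already ask about non-drug care, the detection gap closes and only the article's sentence needs correcting. The exclusion of users after randomization would still deserve the change below.

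**What to change.** 1. **Widen the question.** At each of the 10 sessions, ask every patient, in the same words in both arms, about *any medication or non-drug treatment for the back since the last visit, including heat or cold applied at home*. Record the type and date.
2. **Replace the exclusion sentence**, for drug and non-drug users alike. Suggested text: *Patients who use any prohibited treatment will be asked to stop; the use will be recorded, and they will continue assessments and remain in the primary analysis. Co-treatment will be reported by arm. The primary ANCOVA will be repeated without these patients as a sensitivity analysis only.* This must replace the present sentence; adding it alongside would make the paragraph contradict itself.

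Naming self-applied heat or cold among the banned examples is optional drafting, since the open wording already covers it. Exclusion (iv) can stay as it is.

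**Cost.** Questioning takes slightly longer; no visit is added and eligibility does not change. The second item changes who is analysed while recruitment is under way, so it needs a dated amendment. Patients already treated will lack the non-drug record, and the report should say so. Retaining users may dilute the estimated effect; the sensitivity analysis shows how much the result depends on them, but it does not replace the primary analysis.
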